The study objectives are to: (1) implement injury prevention measures based on safety hazards identified using the CHASE tool within 300 low-income households (at or below 80% Area Median Income) in Baltimore City or County; (2) determine the costs of the injury prevention measures completed by residents and/or professional providers; and (3) conduct a formative evaluation to determine the feasibility of incorporating injury prevention into residential programs from the perspective of installers and residents, including identifying barriers and facilitators, and understand the consistency of implementing and maintaining the injury prevention measures by residents and staff.

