During Phase 2, 300 families will be enrolled. Parents or guardians (or emancipated minors who meet all other inclusion criteria)^1^ whose household is participating in a GHHI home visiting program will be invited to participate. Inclusion criteria include: (1) households with at least one child under 7 years of age or foster care families planning to host a child under 7; (2) the child under 7 years of age lives with the parent or legal guardian most of the time; (3) household income at or below 80% Area Median Income as defined by HUD; and (4) a home address in Baltimore City or Baltimore County.

While scheduling regular GHHI program visits, a GHHI Client Intake Specialist will use a project introduction script and eligibility screening form to briefly introduce the CHASE Implementation Study and review details, including a description of the project services and timeline, and determine if the parent or guardian is potentially interested and eligible to participate. Among those interested and eligible, the Client Intake Specialist will conduct the oral consent process, collect the baseline measures about the family, and schedule the first of three home visits, Home Visit 1 (HV1). Client intake specialist are bachelors trained as professionals whose roles requires customer service and project coordination skills.

HV1 will be scheduled within two weeks after intake. During HV1, a GHHI Assessor will visit the participant’s home, provide a copy of the completed consent form, and ask the study participant to complete a Health Belief Questionnaire. The Assessor will conduct a home inspection using the CHASE Home Assessment Form. After inspecting the residence, the Assessor will transfer assessment details onto the Family Feedback Form. Using this as a guide, the Assessor will then conduct a walk-through of the home providing advice and tailored education to assist caregivers in completing the identified home modifications or calling a contractor to do so on their own. The Assessor will also provide injury prevention supplies, a copy of the Family Feedback Form that lists the hazards identified in the home, and educational materials to assist the participants in completing the recommended modifications within 30 days. With the client’s consent, some photographs may be taken to document hazards identified during the housing assessment; no identifiable people or items will be captured in the phone. Participants may refuse without any negative repercussions.

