Home Visit 2 (HV2) will occur approximately 30 days after HV1. A GHHI Assessor will return to reinspect the home, completing another CHASE Home Assessment Form to identify which hazardous item(s) the participants were able to modify on their own. They will complete a new Family Feedback Form to inform the family about the remaining risks in the home or to communicate that the home has passed all of the CHASE assessment items. A Research Assistant will administer the Health Belief Questionnaire and conduct a Follow-Up Survey.

For participants who were unable to address all hazards identified during HV1 (e.g., because the family could not or did not have sufficient means to address the hazards identified with home modifications alone or by calling a contractor), the Assessor will draft a Scope of Work for completion of the needed modifications and arrange a time to return to the home with the GHHI Housing Intervention Services Team, a professional home modification team who will complete the installation of any incomplete home modifications as described in the Scope of Work.^2^ When modifications are needed outside the capacity of the Housing Intervention Services team, GHHI will arrange for a contractor to complete the Scope of Work. All costs for modifications whether by the GHHI home modification team or by outside contractors will be paid for by the project with the grant funding. As is standard procedure for GHHI, there will be a post-intervention quality control assessment conducted by an Assessor immediately after the injury prevention intervention to verify that all measures on the Scope of Work were installed properly and meet HUD and project standards. Any discrepancies will be resolved. GHHI will document all costs, both labor and supplies, associated with completing the Scope of Work.

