### Data analysis plan

Descriptive statistics and frequency tabulations will be generated on the number of hazards per home at each time point and the total time and cost per home for modifications. Pass scores for the home (number of items passed/total items) will be calculated as well as the prevalence of each individual hazard (out of *N* = 300). The mean, median, and range of costs per household and per injury prevention measure will be calculated. Homes with outliers for the number, duration, and cost of modifications will be identified and the characteristics associated with those homes will be noted. A paired analysis will be used to test the change in mean number of hazards present between HV1 and HV3. Additional analyses will be performed for individual hazards and modifications.

Maintenance of modifications is of particular interest, along with variables that are associated with higher rates of maintenance, which will be examined by comparing HV2 and HV3 data; this will be an analysis of proportion of modifications still in place at HV3 by outcome variable and by modification options. Frequency distributions for the additional variables of interest (sociodemographic characteristics, characteristics of the homes, participant knowledge, participant capacity to complete home modifications, participant satisfaction with the program, and perceived barriers and facilitators collected during the initial home visit by the Assessor) will be prepared. These variables will be used to conduct regression analyses to explain the hazard and maintenance outcomes described above as a function of referral source, sociodemographic characteristics, housing, knowledge, installer (homeowner/tenant and GHHI), and satisfaction. To explore the capacity of caregivers to install injury prevention measures, paired data from HV1 and HV2 will be used to compute change in mean number of hazards.

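### Installer is a property of each modification, but the plan enters it as a two-category term for a per-home hazard outcome; a simple home-level coding without the HV1 count would mislead

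*Protocol article*

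**What the plan says.** The Data analysis plan (Protocol article, Methods) fixes three things.

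- **Hazard outcome, per home.** "A paired analysis will be used to test the change in mean number of hazards present between HV1 and HV3". The descriptive statistics also count hazards per home.
- **Maintenance outcome, built from modifications.** "this will be an analysis of proportion of modifications still in place at HV3 by outcome variable and by modification options".
- **Covariates for both.** The regressions are to "explain the hazard and maintenance outcomes described above as a function of referral source, sociodemographic characteristics, housing, knowledge, installer (homeowner/tenant and GHHI), and satisfaction". The HV1 hazard count is not on this list.

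Procedures (Phase 2) sets who does the work. After HV1 the Assessor gives advice and supplies to "assist caregivers in completing the identified home modifications or calling a contractor to do so on their own". HV2, about 30 days later, records what participants managed themselves. Only where hazards remain does GHHI send "a professional home modification team who will complete the installation of any incomplete home modifications as described in the Scope of Work". There is a further route: "When modifications are needed outside the capacity of the Housing Intervention Services team, GHHI will arrange for a contractor to complete the Scope of Work".

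Objective 2 (end of Background) divides the work differently, aiming to "determine the costs of the injury prevention measures completed by residents and/or professional providers".

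**The concern.** The installer term has two named categories, and one of its two outcomes is a single number per home. The design does not sort homes into resident homes and GHHI homes. Every home has a resident period first, and GHHI then does the remainder in that same home. A mixed home fits neither category.

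The obvious way to force a home-level variable is to ask whether GHHI did any work. That is the same as asking whether the HV2 hazard count was above zero, and homes that start with more hazards are more likely to have one left. Such homes also have more to lose between HV1 and HV3. Installer would then stand in for the starting count.

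Who can do this work is close to the purpose of the study: cost by type of provider, feasibility, and the business case mentioned in the Discussion. An installer coefficient on hazard reduction would be read as evidence on resident versus professional delivery.

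A secondary point is that the two categories do not name contractors, whether called by the family or arranged by GHHI.

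**Working it through.** **1. The plan's own figure.** Sample size gives N = 300, SD 8.4, α = 0.05, 80% power and a detectable change of 1.36. Two-sided: (1.960 + 0.842) × 8.4 / √300 = 1.359. It reproduces and is not in dispute. It refers to the main paired comparison, so it serves below only as a scale.

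**2. How many homes are mixed?** The article gives neither hazard counts nor resident fix rates for CHASE, so both are assumptions. If a home has h hazards at HV1 and residents fix each independently with probability r, then

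P(mixed) = 1 − r^h − (1 − r)^h.

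| h | r = 0.1 or 0.9 | r = 0.3 or 0.7 | r = 0.5 |
|---|---|---|---|
| 3 | 27% | 63% | 75% |
| 5 | 41% | 83% | 94% |
| 8 | 57% | 94% | 99% |
| 12 | 72% | 99% | 100% |

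With fix rates that vary between homes, simulated shares were 48% to 93%.

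**3. Why 'any GHHI work' misleads: a hand example.** Assume half the homes start with 3 hazards and half with 8, r = 0.5, and 20% of fixed items fail by HV3 whoever fixed them.

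- Chance of being resident-only: 0.5³ = 0.125 and 0.5⁸ = 0.0039.
- Mean HV1 count, resident-only homes: (3 × 0.125 + 8 × 0.0039) / 0.1289 = 3.15.
- Mean HV1 count, homes with any GHHI work: (3 × 0.875 + 8 × 0.9961) / 1.8711 = 5.66.
- Difference at HV1: 2.51. False difference in HV1-HV3 change: 0.8 × 2.51 = 2.0 hazards. False difference in HV3 count: 0.2 × 2.51 = 0.5.

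In the same example the expected share of work done by GHHI is 0.5 at both starting counts, so a share coding carries no such artefact.

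**4. Simulations with no true installer effect.** These used 300 homes and 35 items. Assumed inputs were mean HV1 hazards of 5 to 12, fix rates varying between homes, and 15% or 20% relapse regardless of installer, some with a 2% rate of new hazards.

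| Home-level coding | HV1 count in model | False difference in HV1-HV3 change | p < 0.05 |
|---|---|---|---|
| Any GHHI work | no | about 1.3 to 7.9 | 57-100% |
| Majority GHHI | no | −0.3 to +1.5 | 5-69% |
| Any or majority GHHI | yes | about 0 | 0-8% |
| Share by GHHI | no | −0.2 to +0.07 | 4-7% |

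On the HV3 count, unadjusted 'any GHHI' gave +0.3 to +1.4 (15-97%). Where residents fixed few items, only about 2% of homes (roughly 6 of 300) were resident-only, and some datasets could not estimate the coefficient.

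**5. When relapse depends on the household.** Suppose households that fix less also maintain less (relapse 5% to 25%), still with no installer effect. The HV1-adjusted share then gave a false −0.4 to −1.9 hazards on change, significant in 91-100% of those runs. The size depends on how strongly households differ in fixing and maintaining.

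**6. Item level.** Comparing maintenance per modification by installer gave a difference of 0.00 when relapse did not depend on the household.

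**The case against.** The strongest reply is that the article never says how installer is coded for a mixed home, at what unit the regression runs, or whether the HV1 count is included. A condensed article may leave this to the full protocol or analysis plan. The large false effect also needs one particular coding, fitted alone. The plan already foresees analyses of individual modifications, treats maintenance as a proportion of modifications, and examines resident capacity separately through HV1 versus HV2.

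Much of this stands. A reader might infer that every home-level coding produces a spurious installer effect, or that following the plan must do so. The documents support neither: the plan does not state the 'any GHHI' coding, and HV1 adjustment or a share coding brought the artefact to about zero. A reader might also take it as given that most homes are mixed. The article has no such figure, and with few hazards and a very low or very high fix rate the share falls to 27%. Contractors could be assigned to the party that called them, and Objective 2 concerns costs, so its different split is no contradiction.

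What the reply does not remove is the mismatch in the text. The article names the covariate, its two categories and a per-home outcome, and Procedures makes installer vary within homes. The workable remedies, a share or the HV1 count, are not in the stated covariate list.

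**Conclusion.** The point holds in a limited form. For the per-home hazard outcome, the stated installer term does not fit the design. Maintenance is not affected in this way, because installer can be recorded per item.

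The size depends on the coding. A simple 'any GHHI' indicator without the HV1 count gave a false difference of roughly 1.3 to 8 hazards in HV1-HV3 change, mostly above the 1.36 on which the study is sized. With HV1 adjustment or a share coding the artefact disappears, but confounding by household can remain because installer is not assigned. All these sizes rest on assumed hazard counts, fix rates and relapse rates. The main paired test is untouched. The change is worth making because the coefficient would bear on resident versus professional delivery and the remedy is cheap.

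**What to change.** In the Data analysis plan:

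1. Use installer in a modification-level (CHASE item-level) maintenance model with home as the cluster, by random effect or GEE, adjusted for hazard type. Code it per item as resident, GHHI team or contractor, collapsed to resident versus professional if cells are small.
2. Drop installer from the home-level hazard regression, or replace it there with the share of modifications done by GHHI, adjusted for the HV1 hazard count.
3. Report either result as an association, not an effect of who installs. GEE clustering corrects the standard errors but does not remove confounding by household or by difficulty of the item.

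The Scope of Work already identifies items done after HV2. One 'who did this' entry per fixed item in the existing Follow-Up Survey identifies the rest. The cost is that entry, some wording, and the loss of a simple installer coefficient in the hazard-count regression.

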Home Visit 3 (HV3) will occur three months after all safety modifications have been completed. During HV3, a Research Assistant will complete the CHASE Home Assessment Form, the Health Belief Questionnaire, and a second Follow-Up Survey to assess the maintenance and effectiveness of the modifications. The Family Feedback Form will also be completed to inform families of any newly identified or persisting injury hazards, and informational resources will be provided to assist families in addressing identified risks. With the participant’s consent, additional photographs may be taken to demonstrate hazards identified as well as examples of successful repairs. These photographs will be used only for training purposes. We will make sure there are no identifiable people or items in the photographs. The participant can refuse to have photographs taken in their home.

The final phase of the study will involve qualitative interviews with those GHHI staff (Client Intake Specialist, Assessor, and Housing Intervention Services team) who are knowledgeable and experienced with the CHASE program to assess installer perspectives of feasibility, barriers, and facilitators to incorporating injury prevention measures into home visiting programs and sustaining those measures over time. GHHI will provide a list of staff involved in the project to the research team, and the study investigator will email each key informant to invite them to participate in a 30 min one-one-one interview.

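### The maintenance regression compares installers without modification type or time in place, though the visit sequence ties installer to both, and the HV2–HV3 comparison has no in-place baseline for GHHI items

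*Protocol article*

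**What the plan says.** All references are to the protocol article, Methods.

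- **Model.** The Data analysis plan says that regressions will explain the hazard and maintenance outcomes "as a function of referral source, sociodemographic characteristics, housing, knowledge, installer (homeowner/tenant and GHHI), and satisfaction". Other tabulated variables that feed these models include "participant capacity to complete home modifications, participant satisfaction with the program, and perceived barriers and facilitators".
- **Maintenance outcome.** Maintenance and its correlates are a topic "which will be examined by comparing HV2 and HV3 data", and the measure is the "proportion of modifications still in place at HV3 by outcome variable and by modification options". The same section adds: "Additional analyses will be performed for individual hazards and modifications".
- **Who installs what.** Under Procedures, residents have about 30 days after HV1. At HV2 the Assessor reinspects, and homes with hazards still open are passed to "a professional home modification team who will complete the installation of any incomplete home modifications as described in the Scope of Work". For work beyond that team's capacity, "GHHI will arrange for a contractor to complete the Scope of Work". An Assessor checks the installed work immediately afterwards.
- **Timing of the last visit.** "Home Visit 3 (HV3) will occur three months after all safety modifications have been completed".

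**The concern.** Installer is a named explanatory variable with two levels, but a modification's installer is settled by the sequence of visits. An item becomes a GHHI item because it was still open at HV2. If residents tend to complete some kinds of modification and leave others, installer partly stands in for kind of modification.

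The HV3 clock also starts at the last completion in the home. In a mixed home, resident items must therefore survive the wait for GHHI work as well as the three months.

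Finally, a GHHI item is by definition not in place at HV2. If HV2 and HV3 are compared literally, a GHHI item that was installed and then lost looks the same as one never installed.

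What is at stake is how one secondary result is read. The third objective, at the end of the Background, covers how consistently measures are implemented and maintained by residents and staff. A difference in retention produced by item mix or exposure could be taken as a difference between installers.

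**Working it through.** **The plan's own figure.** The only design figure is the detectable change of 1.36 hazards between HV1 and HV3 (Sample size). It reproduces: (1.960 + 0.842) × 8.4 / √300 = 1.36. It does not concern maintenance or installer, so nothing below depends on it.

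**Exposure, from Procedures.** In a home with both installers, let *w* be the time in months from HV2 to completion of the GHHI work. No value is given.

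- Last GHHI item, counted from its quality-control check: 3 months to HV3.
- Resident item, counted from its verification at HV2: 3 + *w* months to HV3.
- Time before HV2 is left out. A resident item enters the HV2–HV3 comparison only if it is present at HV2, and under a constant loss rate its later survival does not depend on its earlier age.
- In a home where residents completed everything, there is no GHHI wait and no excess from this source.

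Assume a constant monthly loss *p*, the same for both installers, so that there is no true installer effect. Retention after *t* months is (1 − *p*)^*t*. Both *p* and *w* are assumptions.

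| *p* | 3 months (GHHI, or resident with *w* = 0) | 4 months (resident, *w* = 1) | 5 months (resident, *w* = 2) | Gap, *w* = 1 | Gap, *w* = 2 |
|---|---|---|---|---|---|
| 2% | 0.98³ = 94.1% | 0.98⁴ = 92.2% | 0.98⁵ = 90.4% | 1.9 points | 3.7 points |
| 5% | 0.95³ = 85.7% | 0.95⁴ = 81.5% | 0.95⁵ = 77.4% | 4.3 points | 8.4 points |
| 10% | 0.90³ = 72.9% | 0.90⁴ = 65.6% | 0.90⁵ = 59.0% | 7.3 points | 13.9 points |

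With *w* = 0 the gap is zero at any loss rate. Gaps are taken before rounding.

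**Item mix.** Take equal numbers of two types, A and B, with retention *m*A and *m*B whoever installs them. Residents complete a share *a* of type A and *b* of type B; GHHI installs the rest.

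- Resident retention = (*a·m*A + *b·m*B) / (*a* + *b*)
- GHHI retention = ((1 − *a*)*m*A + (1 − *b*)*m*B) / (2 − *a* − *b*)

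With *a* = 0.8 and *b* = 0.2 (assumed):

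- If *m*A = 0.70 and *m*B = 0.95: resident 0.56 + 0.19 = 75%; GHHI 0.14 + 0.76 = 90%. GHHI looks 15 points better.
- If *m*A = 0.95 and *m*B = 0.80: resident 0.76 + 0.16 = 92%; GHHI 0.19 + 0.64 = 83%. GHHI looks 9 points worse.

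There is no installer effect in either case. The sign depends on which type lasts longer, and the article does not say.

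**Against the listed covariates.** Referral source, sociodemographics, knowledge, satisfaction and participant capacity describe the family, and housing describes the home. None of them distinguishes two items in the same home by type or by date of completion.

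**The case against.** **Modification type is not absent from the plan.** Maintenance is to be split by modification options, and analyses of individual hazards and modifications are promised. This stands in part: the reader will see retention by type. But neither statement is tied to the installer term, and neither touches time in place.

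**The study does not claim causation.** The Data analysis plan looks for variables associated with maintenance. Study design and setting calls the design non-experimental, and the Discussion says an experimental or quasi-experimental study is still needed. This stands, and it limits the seriousness of the point. Nothing in the article says the installer coefficient will decide who does such work in future. The limitations do not, however, mention unequal item mix or exposure between installers.

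**The exposure gap may be small.** This stands. It depends wholly on a wait that is not given, and it disappears if GHHI finishes at once.

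A reader might also infer more than the documents support:

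- *GHHI gets the items families were unable to fix, so the harder ones.* Only that they were not fixed is certain. The Discussion concedes that families knew GHHI would return, so some items may have been left for that reason. Selection remains, but its nature is unknown.
- *Standard errors will be too small because items cluster in homes.* The article does not state the unit of analysis or that items are treated as independent. The usual inflation formula applies to a covariate constant within home, and installer can vary within home.
- *Installer cannot be used at home level.* It can, for example as the share of items installed by GHHI.
- *Outside contractors have no place in the two-level coding.* The levels can be read as arranged by the household or by GHHI. That definition can be left to a fuller plan.

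**Conclusion.** The concern holds as a structural flaw in a named secondary regression. In homes with both installers, Procedures ties installer to modification type and to time in place, and the stated covariates adjust for neither. The HV2–HV3 comparison also lacks an in-place baseline for GHHI items.

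The size cannot be known from the article. At an assumed 5% monthly loss, the exposure difference alone is worth nothing with no wait, about 4 points with one month and about 8 points with two, always in GHHI's favour. Item mix can add to this or reverse it; the assumed mixes gave +15 and −9 points. The net direction is therefore open, and it would be wrong to conclude that the installer estimate will favour one side, or that any difference found must be spurious.

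The exposure figures assume constant loss. If losses come mostly soon after installation, resident items verified at HV2 have already passed some of that period and GHHI items have not, which works against GHHI. The powered HV1–HV3 comparison is unaffected.

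**What to change.** Amend the maintenance paragraph of the Data analysis plan as follows.

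1. Analyse maintenance at the level of the modification, with a binary model that accounts for clustering on home (GEE or mixed logistic).
2. Include grouped hazard or modification type and time from verified completion to HV3 as covariates beside installer. Broad groups are enough.
3. Define the in-place baseline by installer: HV2 for resident items, and the quality-control check after the intervention for GHHI items.
4. Report the installer contrast as an association, and state in the limitations that items reached GHHI because they were still open at HV2.

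**Cost.** Both verification visits already take place, so the data burden is one verified-completion date per modification. The HV2 date records inspection, not the resident's installation, so the time covariate measures exposure since verification. The statistical price is a less precise installer estimate, particularly where residents and GHHI rarely install the same type or where exposure times overlap little. If overlap is very poor, report retention by type and installer descriptively and do not interpret the coefficient.
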